### Data analysis

Figure 3 shows the between-group (RCT) and within-group (retrospective cohort) comparisons for the outcome measures.

**Figure 3 F3:**
[figure not shown]
Outline of intervention and standard care group comparisons to assess short-term outcomes for the prospective RCT and the retrospective cohort. Mod Risk, moderate risk; Risk Mx, risk management. RCT, randomised controlled trial.

#### Quantitative analysis

Demographic and other cohort features will be examined by descriptive statistics and include tests for heterogeneity between study sites and laboratories. Cohort variables will be compared between the study group and study decliners and with participants who withdraw or do not complete the prescribed assessments at each time point, as well as between the intervention groups.

Risk management and clinical endpoints: Proportions will be examined as above and rates (screening episodes, risk-reducing measures, cancer events) will be analysed by Cox regression and associations between variables and outcomes analysed by regression modelling. To account for multilevel clustering in the data (family, study site, gene, mutation type), a linear mixed model incorporating fixed and random effects corresponding to each level of hierarchy in the data or generalised estimating equation will be used. Predictive accuracy and calibration will be measured by the Matthews Correlation Co-efficient and calibration by a χ^2^ goodness of fit.

Participant experience: Internal consistency of the psychosocial tools will be measured by Cronbach’s alpha coefficient. The impact of variables, including the PRS, on psychosocial outcomes will be analysed in a linear mixed model incorporating data on other stressful life events and accounting for clustering as above.

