## Methods and analysis

### Aims

The primary aim of the trial is to compare the performance of an integrated assessment of breast and ovarian cancer risk that incorporates PRS risk modification, along with personal and familial risk factors, with the current standard of care in a cohort of Australian women undergoing predictive genetic testing for a breast/ovarian cancer gene at an FCC. In the short term, the study will compare the distribution of assessed risk, and risk management recommendations and intentions in the PRiMo intervention group vs the standard care group. In the medium to long term, the study will (i) assess uptake and adherence to risk management strategies and (ii) use follow-up of prospective cancer events to examine the accuracy and calibration of the risk assessment between the PRiMo risk assessment and standard care.

Secondary aims are to assess patient attitudes and experience when undergoing personalised genomic risk assessment for breast and ovarian cancer and to establish the health service implications of implementing PRS-risk-modified assessments in clinical practice including a health economic evaluation.

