### Intervention

Standard care at participating FCCs currently provides risk assessment and risk management advice based on the result of the predictive gene test, along with basic risk factor information based on the national guidelines on cancer risk management for gene carriers.^29^ Where additional personal risk factor information is included, the risk is typically incorporated using the CanRisk tool—a validated online tool to calculate an integrated lifetime breast and ovarian cancer risk.^1 30^ This tool has been shown to be acceptable to clinicians in the genetics setting,^31^ although its use in clinical practice in Australian FCCs was variable at the time the trial commenced. The CanRisk tool is supported by grant PPRPGM-Nov20\100 002 from Cancer Research UK.

The PRiMo intervention is an enhanced breast cancer risk assessment that combines PRS calculated from a combination of common genomic variants with the result of a predictive genetic test and a standard set of basic risk factor information (age, lifestyle risk factors and family history of cancer). This personalised risk assessment is calculated using the CanRisk tool and the output summarised in a custom report that includes the primary genetic information and a risk summary of 5-year, 10-year and lifetime risks for breast and ovarian cancers. In both arms, risk management advice, ongoing follow-up and clinical care will be determined by the participant’s managing FCC and medical team. The retrospective cohort participants have previously tested positive for a moderate-risk gene and had a ‘standard care’ results appointment. Consenting participants in this group will all receive a PRiMo risk assessment and the analysis of the primary study aims will involve comparison of pre-result and post-result questionnaire data for the same women.

The use of PRS in an integrated individualised risk assessment is a novel element in clinical practice. To ensure that clinicians feel confident, and the study intervention is delivered in a standard manner, the trial included development of an education and training programme used with GHPs at participating sites. The programme comprises online learning covering the theoretical aspects of PRS and a facilitated virtual workshop with pre-recorded roleplays and case discussions.^32^

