### Sample

#### Prospective RCT

The trial aims to recruit up to 2000 women undergoing a predictive genetic test for a known familial PV in a gene associated with increased risk of breast cancer: *BRCA1, BRCA2, PALB2, CHEK2, ATM, RAD51C* and *RAD51D*. Eligible participants are 18 to 79 years of age, unaffected by invasive or in situ breast cancer or epithelial ovarian cancer, and able to give informed consent and complete online questionnaires in English.

Exclusion criteria include having had previous genomic testing that included polygenic risk information for breast or ovarian cancer and currently undergoing treatment for a cancer diagnosis.

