### Genomic analysis and PRS

The predictive test is performed by the accredited molecular diagnostic laboratory for each FCC independently of the study and the standard clinical test report is provided to the FCC and the central study team. An additional aliquot of the DNA sample is provided by the diagnostic laboratory for the research genomic analysis.

SNP genotyping is performed on a custom Illumina GSA array. Quality control and genotype calling of the array data are performed using standard bioinformatic packages. Missing genotypes, either due to limitations of the array or issues arising from individual samples, are managed by imputation against the TOPMED and 1000 Genomes whole-genome data sets using standard methodology to optimise the imputation accuracy for each SNP.

Calculation of a breast cancer PRS (BCAC-313) and ovarian cancer PRS (OCAC-36) and generation of the report are performed by the central study team using standard methods developed in the pilot study.^21 22^ Ancestry information is incorporated into the breast cancer risk prediction; information on self-reported ethnicity and published figures on the characteristics of the BCAC-313 PRS score specific to different ancestral groups^25 35 36^ to provide an adjusted Z-score for incorporation into the multifactorial assessment.

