### Randomisation

Randomisation occurs following completion of the pre-test counselling appointment and pre-result baseline questionnaire. Participants in the prospective RCT are randomly assigned to either standard care or PRiMo intervention with a 1:1 allocation as per a computer-generated simple randomisation schedule using the REDCap randomisation module. The trial staff allocating participants do not have access to the randomisation schedule.

To minimise discrepancies in risk advice provided to relatives managed by the same FCC, only the first participant in a family at that site will be randomly assigned to either standard care or intervention. Any related participants that attend the same FCC will be allocated to the same group. Participants will not be informed of this procedure and potential participants will not be aware of their group prior to enrolment.

Given the nature of the intervention, participant and clinician blinding is not possible and both the participant and their FCC will be informed of the outcome following allocation, and procedures for unblinding are not required. Analysis of the primary study aims will be performed without knowledge of the intervention status of each group.

Participants in the retrospective cohort will not be randomised and all will receive the intervention.

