### Statistical considerations and sample size

A power calculation was performed based on the frequency of cancer risk management events in cases and controls—including uptake of recommended strategies and reduction in strategies no longer recommended based on the participants’ risk assessment. Significance is set at p≤0.05 for independent direct comparisons of the two arms, and p≤0.01 after correction for multiple testing for comparisons between subgroups (gene positive; gene negative; and high, moderate and population risk). In the prospective enrolment group, the sample size has power to detect 10% differences in proportions between arms (power for χ^2^ test exceeds α≤0.05, β≥0.8 at 85% of enrolment of prospective group) and power to detect 25% differences in the smallest risk subgroup (moderate risk), accounting for multiple testing. Comparison of the prospective accuracy of PRiMo vs standard care risk assessments was based on a model of the expected distribution of genetic testing results and the PRS that projected an expectation of incident cancers in follow-up. At 3 years mean follow-up, the full sample will be powered to detect a 10% increase in the proportion of breast cancers detected in the high-risk group; that is, a greater proportion of the breast cancers detected in follow-up will occur in the high-risk women in the intervention arm than in the standard care arm (β=88%, α=0.05, on a test for superiority). The sample for retrospective recruitment was based on the number of families with an identified PV in *PALB2*, *ATM* or *CHEK2* in Australia.

For the secondary aims, the proposed study size correlates to more than adequate statistical power (β>90%, α=0.01) to detect differences in the questionnaire outcomes. Consideration will be given to both the statistical and clinical significance of any differences.

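### Accuracy is powered on each arm's share of breast cancers in its own high-risk women, which is sensitivity alone; the 88% power could not be reproduced, and a within-woman comparison would answer the question better

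*Protocol article*

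**What the plan says.** - Aims: as a medium- to long-term part of the primary aim, the trial will "use follow-up of prospective cancer events to examine the accuracy and calibration of the risk assessment between the PRiMo risk assessment and standard care".
- Statistical considerations and sample size: at a mean of 3 years, the full sample has 88% power (alpha 0.05, superiority) for a 10% increase in the share of breast cancers found in the high-risk group. This is spelled out as a larger share that "will occur in the high-risk women in the intervention arm than in the standard care arm". The event projection is attributed to a model. Neither the number of cancers, nor the control share, nor the sidedness is printed.
- Quantitative analysis: "Predictive accuracy and calibration will be measured by the Matthews Correlation Co-efficient", with a chi-square goodness of fit for calibration.
- Prospective RCT (sample): "The trial aims to recruit up to 2000 women undergoing a predictive genetic test". Randomisation: "with a 1:1 allocation as per a computer-generated simple randomisation schedule", where "only the first participant in a family at that site will be randomly assigned" and later relatives at that site take the same arm.
- Design and setting: standard-care women may receive the PRiMo assessment one year after their results.
- Introduction: risk-reducing measures are described as effective. Intervention: the clinic decides management in both arms. It also says of CanRisk, "although its use in clinical practice in Australian FCCs was variable at the time the trial commenced".

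**The concern.** The powered comparison asks what fraction of each arm's cancers arose in women that arm had called high-risk. This is sensitivity, with no penalty for labelling more women. A looser label in the intervention arm would therefore pass for better accuracy.

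The label also changes the outcome. High-risk women may be screened more, so more cancers are found, or may take risk-reducing action, so fewer occur. From one year, standard-care women may receive the intervention's assessment while follow-up continues. The comparison thus mixes prediction, labelling rate and management.

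Few cancers are likely in three years, and splitting them between arms leaves little information. At stake is whether the accuracy part of the primary aim can be interpreted, whichever way the result falls.

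**Working it through.** **1. A stated power that does reproduce.** Risk-management proportions, 850 women per arm (85% of 1000), 10-point difference, two-sided 0.05: power is at least 0.985 for control rates of 5% to 45%. The claim of at least 0.8 is confirmed.

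**2. The 88%.** The denominator is cancers per arm, n. With d = 0.10 and p̄ the mean of the two shares:

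n = [z_α√(2p̄(1−p̄)) + z_0.88√(p₁(1−p₁)+p₂(1−p₂))]² / d²

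For 70% vs 80%, two-sided: [1.960×√0.375 + 1.175×√0.37]² / 0.01 = (1.200 + 0.715)² / 0.01 ≈ 367. Power at a given n inverts the same formula.

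| Shares | n per arm for 88%, two-sided | one-sided | Two-sided power at n = 21 | 33 | 58 |
|---|---|---|---|---|---|
| 30 vs 40% | 446 | 361 | 0.10 | 0.13 | 0.20 |
| 50 vs 60% | 485 | 392 | 0.09 | 0.13 | 0.19 |
| 70 vs 80% | 367 | 297 | 0.11 | 0.15 | 0.24 |
| 80 vs 90% | 249 | 202 | 0.14 | 0.20 | 0.32 |
| 89 vs 99% | about 109 | about 88 | 0.27 | 0.40 | 0.62 |

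One-sided, 89 vs 99% gives 0.39, 0.53 and 0.74 at 21, 33 and 58 cancers.

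**3. How many cancers are plausible.** The Introduction gives lifetime risks of 50% to 70% for BRCA1/2 carriers and 14.3% as near population level. Assume a flat hazard over 60 years, h = −ln(1−L)/60:
- L = 14.3%: 0.00257 per year; L = 50%: 0.01155; L = 70%: 0.02007.
- Half at 14.3%, half at 50%: mean 0.00706, so 1000×(1−e^(−3×0.00706)) ≈ 21 cancers per arm.
- Half at 14.3%, half at 70%: mean 0.01132, about 33 per arm.
- Every woman at 70%: about 58 per arm, an upper bound.

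Adding the 400 non-randomised retrospective women (1200 per arm, all at 70%) gives about 70 per arm and 0.81 in the most favourable one-sided case. Values near 88% appeared only under tests the text does not describe: a one-sample test against a fixed 89% with 40 cancers, or 1000 women rather than cancers as the denominator (60 vs 66%, one-sided, 0.87). No allowance was made for family clustering, which would lower power.

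**4. Label frequency.** Assume the standard label covers 35% of women and 70% of cancers. Label a further 10% of women at random from the other 65%: the share becomes 0.70 + 0.30×10/65 = 0.75. In a simulated model (3-year incidence about 1.9%), a PRS of no value with 45% labelled gave 0.79, close to the 10-point target.

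**5. The Matthews coefficient.** With sensitivity s, labelled fraction q and incidence π:

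MCC = (s − q)√(π/(1−π)) / √(q(1−q))

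- s = 0.70, q = 0.35, π = 0.019: 0.35×0.139/0.477 = 0.102.
- The valueless PRS at q = 0.45 gave 0.095, so the coefficient fell while the share rose.
- A random label (s = q) gives 0 at any q.

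The formula depends on q and π, so arms that differ in label rate or incidence are not comparable on it. At about 38 cancers in total, the simulated between-arm difference was 0.005 with SD 0.046 (power about 3%).

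**6. Risk-reducing action.** Assume equal label rates, an informative PRS (share 0.73 vs 0.70) and a hazard cut in labelled women of 40% in intervention and 20% in standard care. The shares become 0.73×0.6/(0.73×0.6+0.27) = 0.62 (0.61 in simulation) and 0.70×0.8/(0.70×0.8+0.30) = 0.65. MCC was 0.064 vs 0.082. The better score looks worse.

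**7. Scoring every woman both ways.** Let b and c be the fractions of all cancers that PRS moves into and out of high risk, with b − c = 0.10. McNemar power is Φ{[(b−c)√N − 1.96√(b+c)] / √(b+c−(b−c)²)}. For assumed (b, c) of (0.12, 0.02), (0.15, 0.05) and (0.20, 0.10):
- N = 42: 0.41, 0.30, 0.21.
- N = 67: 0.59, 0.45, 0.32.
- N for 88%: 134, 193, 292.

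This is roughly two to four times the between-arm power, but short of 88%.

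**The case against.** - **The coefficient.** A reader might infer that it too is inflated by labelling more women. Step 5 shows it is not; that fault belongs to the share in the sample-size section. Nor does the article say the coefficient is computed separately by arm on each arm's own label. It may be applied otherwise, and the Aims wording does not exclude scoring women both ways. The between-arm construction is explicit only in the power statement.
- **Power.** A reader might infer that 88% is impossible. That is not shown: the event count and control share are unprinted, and a control share near 90% with many cancers raises power considerably. What stands is that no input supported by the article's own lifetime risks reproduced 88% for 2000 women under the test described.
- **The gain from pairing.** Simulations with 36 to 56 cancers gave 51% to 90% power for the PRS term over the no-PRS risk (PRS hazard ratio 1.4 to 1.6 per SD), against 2% to 6% for the between-arm share. These are different hypotheses, and the 2% to 6% is power at simulated gains of 0.4 to 5.4 points, not at the stated 10. The like-for-like gain is step 7.
- **The comparator.** CanRisk without PRS is not exactly usual care, and scoring both ways does not undo the effect of risk-reducing action. Both objections stand and are carried into the fix.
- **Scope.** Cancer events are also analysed by Cox regression, so censoring is not ignored throughout. An unseen analysis plan may settle horizons and models. The stated endpoint and power claim remain.

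**Conclusion.** The point holds for the powered accuracy comparison. The share of cancers in each arm's high-risk women measures sensitivity only, moves with the labelling rate, and is altered by label-driven management and crossover. Its 88% power is not reproduced: about 250 to 485 cancers per arm are needed two-sided at control shares of 30% to 80% (about 109 at 89%; 88 to 392 one-sided across all these shares). About 21 to 33 are plausible and 58 is the upper bound. Power is then 0.09 to 0.20 at 21 to 33 cancers and those control shares, and at best 0.74 (89 vs 99%, one-sided, 58 per arm). These figures assume 1000 women per arm, a flat 60-year hazard, half the women carriers (except at the upper bound) and an absolute 10-point gain.

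The Matthews coefficient is a poor main measure for a narrower reason. It needs a binary label and a known outcome, depends on threshold and prevalence, and discards continuous risk and censoring. The chi-square calibration test has a related weakness: a standard-care woman need not have a numeric prediction.

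Accuracy is one component of the primary aim. The power for risk-management proportions is unaffected.

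**What to change.** 1. Make the main accuracy analysis a within-woman comparison, in all randomised women with a PRS, of centrally computed CanRisk breast cancer risk without and with PRS at a 3- or 5-year horizon. State that the no-PRS score is a fixed rule standing in for the standard assessment.
2. Report the difference in time-dependent AUC, the PRS term in a Cox model with the no-PRS risk as offset, and the observed/expected ratio and calibration slope for each score.
3. Stratify by arm and account for family clustering. Censor at bilateral mastectomy or death, add a sensitivity analysis for other risk-reducing action, and repeat in standard-care time before crossover.
4. Keep the between-arm share and the Matthews coefficient as descriptive only.
5. Withdraw the 88%, or restate it with the expected cancers, control share and sidedness.

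The inputs are largely in hand. Table 1 lists risk factors, pedigree and gene result before results are given, and "An additional aliquot of the DNA sample is provided by the diagnostic laboratory for the research genomic analysis", with no restriction by arm.

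Costs: central CanRisk runs; genotyping stored DNA of standard-care women who do not cross over, where not already done (or restricting to women with a PRS); a comparator that is not exactly usual care; residual distortion from risk-reducing action; and giving up a favourable power figure that pairing does not restore.

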#### Qualitative analysis

Interviews and focus groups will be transcribed and thematic analysis performed to examine perceived benefits and obstacles to testing perceived priorities, determinants for future clinical implementation, and the strategies, tools or resources that may be required. Initial results may inform the content of questionnaires at later study timepoints.

#### Microsimulation of long-term outcomes and healthcare implications

Primary outcome data from the follow-up and questionnaire data will be used to perform simulation of long-term (lifetime) outcomes to examine the practice implications for the Australian public healthcare system. The analysis uses miBRovaCAre, a complex model (a discrete-time, state-based microsimulation, with annual cycles) of high-risk management for breast and ovarian cancer^39^ that has been validated against prospective outcomes for the management of carriers of *BRCA1* and *BRCA2* PVs.^14^

#### Cost-effectiveness analysis

The longitudinal quality-of-life scores from the AQoL-8D (validated in an Australian setting and responsive to psychosocial measures^40 41^) will be used with ‘cost of care’ data gathered from linkage to the MBS, the PBS, hospital costs from government data and the main study outcomes, to evaluate the most effective and cost-effective care pathways for women at different levels of current and future breast cancer risk. The outputs include life-years and quality-adjusted life-years saved, healthcare costs associated with the intervention and the incremental cost-effectiveness ratio. The impact of uncertainty on model outputs will be assessed using one-way and probabilistic sensitivity analyses.

### Patient and public involvement

Collaboration with consumers and community members has been integral to the design of the study. Two participants in the pilot project of PRS-based assessment have acted as consumer advisors for the development of the trial and the final research plan. Consumer input was sought in the design of patient study materials and we have engaged a Consumer Advisory Panel to provide advice on the trial and dissemination of the study findings.

### Data management, monitoring and access

Study data will be collected and managed using the REDCap electronic data capture tools hosted at Peter MacCallum Cancer Centre. To promote data quality and participant retention, data collection forms include a range of checks and branching logic, and participants will be allowed to skip questions. Automated email and SMS reminders will be used, and participants will be invited to complete questionnaires at all timepoints, regardless of whether previous questionnaire(s) have been completed.

On written request, the full protocol, metadata and deidentified study data (excluding data provided by Services Australia), from participants who give permission for their data to be used for related future research projects can be made available to research collaborators contingent on approval by a Human Research Ethics Committee and the trial steering committee.

A trial steering committee meets 2 monthly to oversee study planning and progress and review adverse events and unintended consequences reported by site investigators to the central study site. Given the low-risk intervention, there will not be an additional independent Data Monitoring Committee.

